**PROTOCOL SYNOPSIS**

| **Objectives** | Evidence-based medical research methods are used to explore the clinical efficacy and safety of long-term use of Qiliqiangxin capsule with cardiovascular mortality and incidence of re-hospitalization for recurrence of heart failure as main study endpoints, in order to determine its curative effects and target group, and provide high quality clinical evidence for optimizing clinical drug regimen. | |
| --- | --- | --- |
| **Study design** | Randomized, double-blind, placebo-controlled, multicenter clinical trial | |
| **Target patient population** | **Inclusion criteria:**   1. Provision of signed informed consent prior to any study specific procedures; 2. Male or female, aged ≥18 years at the time of consent; 3. Established documented diagnosis of heart failure for at least three months ago according to “Chinese Heart Failure Diagnosis and Treatment Guideline” issued by the Chinese Medical Association Cardiovascular Branch. 4. Left ventricular ejection fraction (LVEF) ≤40% (echocardiogram, radionuclide, ventriculogram, contrast angiography or cardiac MRI ); 5. NYHA cardiac functional grading II to III, with stable clinical symptoms; including those diagnosed as grade IV within 2 weeks before enrollment; 6. Serum NT-proBNP ≥ 450pg/ml; 7. Those who have received standardized baseline treatment regimens without doses adjusted and given intravenously for at least two weeks prior to enrollment;  - standardized drug treatment includes: angiotensin-converting enzyme inhibitor (ACEI) or angiotensin receptor blocker (ARB) or angiotensin receptor neprilysin inhibitor (ARNI), beta blocker, and aldosterone receptor antagonist (the optimal therapeutic dose should be achieved, except for contraindications or intolerance);   **Exclusion criteria:**  Patients should not enter the study if any of the following exclusion criteria are fulfilled   1. Heart failure caused by valvular disease, congenital heart disease, pericardial disease, arrhythmia or non-cardiaogenic disease, or caused by vital organ failure (such as renal, hepatic failure, etc.); and right heart failure caused by pulmonary or other definite causes; and acute heart failure; 2. Coronary revascularization (percutaneous coronary intervention [PCI] or coronary artery bypass grafting [CABG]) or cardiac synchronization therapy planned to undergo after randomization, or had received cardiac resynchronization therapy prior to enrolment; 3. Any condition outside the CV diseases such as but not limited to malignant tumor, severe mental illness, hematopoietic diseases, neuroendocrine system disease, liver transaminase and alkaline phosphatase ≥ 3 x upper limit of normal (ULN), abnormal renal function serum creatinine > 2 mg/dl (176.82 umol/L), potassium >5.5mmol/L; 4. Patient with left ventricular outflow tract obstruction, myocarditis, aortic aneurysm, aortic dissection, or obvious hemodynamic changes caused by unrepaired valve; 5. Cardiogenic shock, uncontrollable malignant arrhythmia, sinus or atrioventricular block at second degree type II or above without pacemaker treatment, progressive unstable angina pectoris or acute myocardial infarction; 6. uncontrolled hypertension systolic blood pressure (SBP) ≥ 180mmHg and/or diastolic blood pressure (DBP) ≥ 110mmHg; or SBP < 90mmHg and/or DBP <60mmHg; 7. Participation in another clinical study with an IP during the last month prior to enrolment; 8. Women of child-bearing potential (i.e., those who are not chemically or surgically sterilized or who are not post-menopausal) who are not willing to use a medically accepted method of contraception that is considered reliable in the judgment of the investigator, from the time of signing the informed consent throughout the study and 4 weeks thereafter, OR women who have a positive pregnancy test at enrolment or randomization OR women who are breast-feeding;   10）Allergic constitution; known to be allergic to research drug;  11）Inability of the patient, in the opinion of the investigator, to understand and/or comply with study medications, procedures or any conditions may render the patient unable to complete the study. | |
| **Outcome Measures** | Primary endpoints | The composite endpoint events consisting of cardiovascular death and re-hospitalization due to the worsening of heart failure |
| Secondary endpoints | 1. All-cause mortality 2. Secondary endpoint events (given up treatment due to worsening heart failure, successful resuscitation after cardiac arrest, malignant arrhythmia, non-fatal stroke) 3. The incidence of cardiovascular death and re-hospitalization due to worsening heart failure in patients with ischemic heart disease 4. Serum NT-proBNP decrease rate |
| Safety objective and measure | To evaluate the safety and tolerability of QLQX in this patient population;  Changes in clinical chemistry/haematology parameters, ECG, physical examination, any forms of adverse events (AEs) |
| **Statistical methods** | The primary objective of the study is to determine the superiority of QLQX versus placebo in reducing the incidence of the primary composite endpoint. The random distribution ratio is 1:1 between study group and control group. The sample size is in estimating the incidence of composite endpoint events for 25% during the follow-up period of 36 months. In total 3080 cases were expected to enroll (1540 patients per group) with 620 composite endpoint events should be observed. | |
| **Statistical unit** | Peking University Clinical Research Institute | |
| **Dosage and mode of administration** | Study group: Standardized treatment of chronic heart failure + Qiliqiangxin Capsules, 4 capsules/time, 3 times/day, take orally  Control group: Standardized treatment of chronic heart failure + Placebo Capsules, 4 capsules/time, 3 times/day, take orally | |
| **Duration of treatment** | The patient was enrolled with observation event as the index. The planned enrollment time was 2 years and the drug was taken for at least a year. | |
| **Expected progress** | August 2018 to August 2021 | |

# 1. Introduction

# 1.1 Study Topic

Qiliqiangxin in Heart FailUre：AssESsment of Reduction in MorTality (QUEST study)

# 1.2 Study Purpose

Evidence-based medical research methods are used to explore the clinical efficacy and safety of long-term use of Qiliqiangxin capsule with cardiovascular mortality and incidence of re-hospitalization for recurrence of heart failure as main study endpoints, in order to determine effective characteristics and suitable population, and provide high quality clinical evidence for optimizing clinical drug regimen.

# 1.3 Study Background

Cardiovascular disease is one of the major causes of death globally, seriously threatening human life and health [1, 2]. Chronic heart failure (CHF) is a series of clinical syndromes caused by pump failure, reduced ejection fraction, circulatory congestion and/or a series of neurohormonal changes on the basis of structural and/or functional abnormality [3]. As a serious stage of various heart diseases, epidemiological studies showed that the number of global heart failure patients has reached 22.5 million, and the 5-year survival rate is similar to malignant tumors.

With the changes of epidemiology and the development of social economy, the epidemiological characteristics of heart failure in developing countries are becoming similar with those in developed countries. For instance, coronary heart disease is becoming the main cause of heart failure in China [4, 5]. In recent years, the European Society of Cardiology (ESC) make a statistical study in 51 countries and has found that there are at least 15 million heart failure patients in about 1 billion people. In 2007, the American Heart Association (AHA) reported that the number of heart failure patients has exceeded 5 million in the United States, and is still increasing at a rate of 550,000/year [6]. The incidence is Japan, which has similar geographical location and ethnic group characteristics as China, is similar to that in Europe and the United States. In 2003, GU Dongfeng *et al* randomly surveyed 15,518 adults (aged 35-74 years old) in respective five provinces and cities in the south and north of China, and found that the prevalence of heart failure in China was 0.9%, including 0.7% for men and 1.0% for women [7]. The incidence and prevalence rate are also gradually increasing worldwide; the number of heart failure patients is increasing at a rate of 2 million per year.

Due to the economic improvement, diet change, and also the extending of human life, the incidence of heart failure increases with age [8]. Also, with the development of modern medicine, the mortality rate of patients with heart failure has gradually decreased, but remains in a relatively high level. The 1-year mortality rate of patients with heart failure over 70 years old is significantly higher than that of patients under 70 years old (22%: 13.7%) in the United States [9]. The 1-year and 3-year mortality rates of heart failure patients are 11.3% and 29.2% in Japan, respectively [10]. In Europe, the 4-year survival rate is only 50%, and 40% of heart failure inpatients is admitted to hospital for treatment or dies within 1 year [11, 12]. Chronic heart failure is still a major problem that seriously threatens human life and quality of life which in need to be resolved.

In the past 20 years, the concept of drug treatment for heart failure has changed greatly, from the perspective of improving hemodynamics to the point of biological adjustment. The focus of modern treatment models is to improve the neuroendocrine disorders of the renin- angiotensin-aldosterone system and the sympathetic nervous system. Therefore, the goal of treatment is not only to improve symptoms and quality of life, but also to inhibit and delay the development of myocardial remodeling, terminate the vicious circle, thereby to reduce the mortality and hospitalization rate of heart failure.

Myocardial remodeling is the basic mechanism of heart failure, including pathological cardiomyocyte hypertrophy with re-expression of embryonic genes, cardiomyocyte apoptosis and necrosis, and excessive deposition or degradation of myocardial extracellular matrix. Slowing or preventing myocardial remodeling is of great value in preventing and controlling the occurrence and development of heart failure and improvement of cardiac function. Activation of two neuroendocrine systems, including sympathetic nervous system (SNS) and renin-angiotensin-aldosterone system (RAAS), and myocardial remodeling promote each other and aggravate the development of heart failure. ACEI, beta blockers, ARB and aldosterone receptor antagonists are shown to be beneficial, indicating the effectiveness of inhibiting these two systems. However, the mechanisms of heart failure are not limited to the SNS and RAAS, further research are needed to explore the effective anti-heart failure pathways, and infer new targets for treating heart failure.

Numbers of clinical studies in the late 1980s also confirmed that activation of neuroendocrine system leads to myocardial remodeling, which is a key factor in the occurrence and development of heart failure. In 1987, CONSENSUS, a clinical trial of angiotensin-converting enzyme inhibitor (ACEI) for heart failure, successfully reduced the total mortality of heart failure patients by 27%. Later, clinical trials such as SOLVED and V-HeFY further confirmed that ACEI can effectively improve prognosis of heart failure.

In the mid-to-late 1990s, CIBISII, MERIT-HF and COPERNICUS studies confirmed that beta blockers reduced mortality in heart failure patients by 34% to 35%. In addition, the RALES trial (1999) and EMPHASIS-HF (2011) studies had shown that aldosterone receptor antagonists can reduce mortality in heart failure patients by 24% to 30%.

New drugs that have benefited patients with heart failure since 2010 are mainly ARNI and cardiac sinus node inhibitors. In the PARADIGM-HF trial, 8442 heart failure patients with reduced ejection fraction (HFrEF) were randomized to receive ARNI and enalapril. The incidence of primary endpoints (cardiovascular death and hospitalization for heart failure) was 21.8% in ARNI group, significantly lower than the enalapril group (26.5%) [13]. The SHIFT study showed that the relative risk of hospitalization for cardiovascular death and worsening heart failure was reduced by 18% compared with the standard treatment group, and left ventricular function and quality of life were significantly improved [14] . At the same time, clinical research has also found that diuretics can effectively relieve dyspnea in patients with heart failure. Rational use of diuretics is the key and foundation for other successful treatment of heart failure by eliminates fluid retention, improves heart function and exercise tolerance.

During this period, non-pharmacological treatment of heart failure has also made important progress. Choosing the suitable patient based on drug treatment can further improve the heart function and quality of life and reduce mortality.

Despite some progress in the field of heart failure treatment in these years, the current prevalence and mortality of heart failure remain high. There is still a need to develop new treatments and develop new drugs to achieve breakthroughs in heart failure treatment.

Traditional Chinese medicine (TCM) has accumulated rich experience in the long-term medical practice of preventing and treating heart failure, and its understanding of heart failure is also deepening. There have been some researches and reports on the treatment of heart failure with TCM. The researches on the treatment of heart failure by Chinese medicine QiliQiangxin Capsules was initially successful. The research results were published in an international journal of cardiovascular disease JACC in 2013[15] and received the attention and praise from worldwide scholars. All enrollees were treated with standard-optimized treatment, and the ratio of serum amino-terminal B-type natriuretic peptide precursor (NT-proBNP) was significantly lower in the Qiliqiangxin capsule group compared with the placebo group, higher ratio of patients with a decrease of >30% and lower incidence of adverse events were observed, indicating that Qiliqiangxin Capsules is effective and safe in the treatment of chronic heart failure. Qiliqiangxin Capsules became the first proprietary Chinese medicine to be included in the Guidelines for the Diagnosis and Treatment of Heart Failure in China 2014 and 2018.

Qiliqiangxin Capsules is the first to explore the pathogenesis and treatment of chronic heart failure with the theory of collateral disease, which proposes insufficiency of the heart-qi as the basis of TCM. Meanwhile, obstruction of collaterals is the central link. The fluid does not flow and exudes from veins which the blood stasis and water stasis blocks the veins, inducing edema [16]. The theory is similar with a new concept proposed by modern medicine in recent years that the hemodynamic changes caused by early neuroendocrine activation can lead to ventricular remodeling, which is the basic mechanism for the development of heart failure.

Due to the post-marketing unique advantages of Qiliqiangxin Capsules in the clinical application, it has become a hot spot for many experts and scholars in China. Previous studies have shown that the drug has cardiotonic and diuretic effect, can improve the heart function of CHF rats, and increase water discharge by reducing the expression of AQP2 in the kidney [17]. It also can reduce the expression of AngII and periostin proteins in rats with heart failure after myocardial infarction and is dose-dependent [18]. The mechanism of the effect of Qiliqiangxin Capsules on improving cardiac function is related to its inhibition of myocardial remodeling [19]. Reducing the pro-inflammatory factors of cardiomyocytes and increasing the immunomodulatory effects of anti-inflammatory factors may be one of the immunopharmacological mechanisms of Chinese medicine for improving heart function in AMI rats [20]. In the clinical study of taking Qiliqiangxin Capsules for the treatment of patients with chronic congestive heart failure, it is indicated that Qiliqiangxin Capsules can improve cardiac function grading, heart failure (Lee’s) score, systolic and diastolic function, ejection fraction (EF), TCM syndrome differentiation (中医证候), quality of life and other curative indicators and safety indicators, elevate blood nitric oxide (NO) and calcitonin gene-related peptide (CGRP) levels, and decrease endothelin (ET) levels; thereby significantly improving endothelial function in patients with heart failure.

In summary, Qiliqiangxin Capsules could resolve the current problems and eliminates the essential causes that treat cardiac insufficiency from multiple pathways, multiple links and multiple targets. It reflects the advantages of compound Chinese medicine in treating heart failure from the overall treatment, and significantly reduces NT- ProBNP levels, indicating improvement of the patient's long-term prognosis. This study is a large randomized, double-blind, multi-center clinical study carried out on the basis of achieving major study results with NT-proBNP as a surrogate endpoint, adopts the incidence of composite endpoint events consisting of cardiovascular death and re-hospitalization for heart failure as the study endpoints, in order to collect the evidence-based medical evidences for long-term prognosis in patients with chronic heart failure.

# 2. Study design

# 2.1. Rationale for study design

This study is a randomized, double-blind, placebo-controlled, parallel-group, multicenter clinical study.

The study will be event-driven, and all randomized patients will remain in the study (whether taking the study drug or not) until the number of primary endpoint events reaches the predicted value (620 cases), or the study terminates early when it meets the pre-defined efficacy or safety criteria of early termination.

Two mid-term efficacy analyses planned to be conducted after 1/2 and 2/3 primary endpoint events to assess whether an invalid or valid conclusion was reached so as to prematurely end the study.

The entire study will last approximately 36 months, and the recruitment period will be expected to be 24 months. The follow-up period after the last case of patient is included in the study is 12 months. The average follow-up time is predicted to be about 24 months.

Patients who show stable clinical symptoms, had received at least 2 weeks of standardized treatment and treatment of other concomitant diseases before enrollment are screened at the hospital. According to the local HF treatment guidelines, the drug type and dosage are fixed, unless it is contraindicated or intolerant. The patient who have not receive anti-HF drug intravenously for at least two weeks prior to enrollment, nor take oral administration of TCM or Chinese patent medicine having similar composition with Qiliqiangxin Capsule can directly enter the random grouping stage.

If patients fail to meet the above requirements, term standardized treatment to meet the above criteria before entering the random grouping stage are needed.

# 2.2. Control group and Sample size

According to the PARADIGM-HF study, cardiovascular death or hospitalization rate for heart failure in the median follow-up of 27 months was 21.8% in the LCZ696 group and 26.5% in the Enalapril group. Therefore, we estimate that the incidence of cardiovascular death and hospitalization for heart failure is 25% in all patients of basic treatment +placebo group within 36 months of follow-up and 20% in basic treatment + Qiliqiangxin Capsule group.

The random distribution ratio is 1:1 between study group and control group. Considering the consumption of type I error in the interim analysis, α is adjusted to unilateral 0.02314. The sample size is the number of cases with composite endpoint events. It is expected that 620 composite endpoint events need be observed to provide 80% power of test (β= 0.2), and 20% risk can be reduced in study group by log-rank test.

The entire study will last approximately 36 months to follow up, and the recruitment period are expected to be 24 months. It is expected that 3,080 patients in over 100 centers (1540 patients per group, 1:1 into study group and control group) will be enrolled and be followed up at least for 12 months. Estimating the incidence of composite endpoint events is 25%, in total 620 end-point events are expected to be obtained in the analysis.

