# 3.2.2 Randomization and Treatment period (day 0 to 12 months [with maximum of 36 months]):

The dispensing date of the IPs is regarded as day 0. Patients will be randomized into the study or control group in a 1:1 ratio w

ith the basis of current standardized treatments for chronic heart failure. The study drug is recommended to be taken about 30 minutes after meals, three times a day as follow.

-Study group: Standardized treatment of chronic heart failure + Qiliqiangxin Capsules (4 capsules/time, 3 times/day);

-Control group: Standardized treatment of chronic heart failure + Placebo Capsules (4 capsules/time, 3 times/day);

This study does not allow dose adjustments. If the patient miss to take the IP in a day, the accumulated dose for the next day should not exceed the daily dose. If the patient has an intolerable adverse event, which is relevant to study drug according to the judgment of researcher, the patient should terminate the following treatment with the study drug.

Do not take drugs at home on the morning of visit day. Investigators will review laboratory results received from the past visit(s). If the patient has experienced any potential endpoints, SAEs, DAEs and/or AEs of interest since the last visit, these should be recorded in the CRF.

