# 13. Study timetable and end of study

| July 2018 | Complete development of study programme, and hold preparatory meeting |
| --- | --- |
| September 2018 | Modify plan and pass ethical audit |
| October 2018 | Study drug and data preparation |
| January 2019 | International registry of the study and start-up of sub-centers |
| March 2019 | Select and enroll the first case |
| October 2020 | Complete randomized grouping of all cases |
| October 2021 | Complete follow-up of all cases in each center |
| December 2021 | Complete data entry and blind review |
| April 2022 | Statistical analysis |
| June 2022 | Complete the study summary report |

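### The 25% and 20% risks, as stated at 36 months, give about 478 primary events by month 36, not 620; reaching 620 would take about 44 months

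*Protocol*

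**What the plan says.** Section 2.2 gives the assumed risk of the primary composite as "is 25% in all patients of basic treatment +placebo group within 36 months of follow-up and 20% in basic treatment" plus the study capsule. The synopsis repeats the placebo figure on the same time base: "estimating the incidence of composite endpoint events for 25% during the follow-up period of 36 months". Section 2.2 then sets one-sided alpha at 0.02314, asks for 80% power by log-rank test for a 20% risk reduction, and puts the requirement at 620 events. It plans 3,080 patients (1,540 per group), 24 months of recruitment, at least 12 months of follow-up and about 36 months overall, and closes: "Estimating the incidence of composite endpoint events is 25%, in total 620 end-point events are expected to be obtained in the analysis".

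Section 2.1 gives the same calendar and adds: "The average follow-up time is predicted to be about 24 months". It also makes the study event-driven: randomised patients stay in until 620 primary events have occurred, unless a predefined early-termination criterion is met.

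Two other places carry durations. The heading of section 3.2.2 describes the treatment period as "day 0 to 12 months [with maximum of 36 months". The section 13 timetable has the first patient in March 2019, "Complete randomized grouping of all cases" in October 2020, and follow-up complete in October 2021. That is about 19 months of accrual and 31 months in total.

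**The concern.** A 36-month risk applies in full only to patients followed for 36 months. With recruitment spread over 24 months and a close at about month 36, only the first patients reach that horizon; the last are followed for 12 months. The events expected by month 36 must therefore be well below 25% and 20% of the two groups. Yet the protocol expects 620, exactly the number it says it needs.

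At stake is the planning basis of the trial. The event rate and the calendar determine how long the study runs, how much drug and funding it needs, and when the two interim analyses (after 1/2 and 2/3 of the events, section 9.3) fall. If the rates are right as written, the stated duration is too short. If the duration is right, the rates carry the wrong time base. A second looseness compounds this: 25% versus 20% and a 20% risk reduction by log-rank test are different hazard ratios, and the protocol does not say which one the 80% power refers to.

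**Working it through.** **Inputs (sections 2.1 and 2.2).** Risks 25% and 20% at 36 months; 1,540 patients per group; accrual A = 24 months; study length T = 36 months; one-sided alpha 0.02314 (z = 1.993); power 80%; 620 events. The protocol gives no dropout rate, so none is applied at first.

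**1. Trying to reproduce 620 by simple products.**
- 25% × 3,080 = 770.
- 1,540 × 0.25 + 1,540 × 0.20 = 385 + 308 = 693.
- 620 / 3,080 = 20.1%, which is not 25%.

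**2. Expected events on the literal reading.** With exponential event times:
- placebo hazard = −ln(0.75)/36 = 0.00799 per month;
- active hazard = −ln(0.80)/36 = 0.00620 per month.

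Under uniform accrual, the probability of an event by time T is P = 1 − [exp(−λ(T−A)) − exp(−λT)] / (λA).
- Placebo: 1 − (0.9086 − 0.7500)/0.1918 = 0.173, and × 1,540 = 266.8.
- Active: 1 − (0.9283 − 0.8000)/0.1488 = 0.137, and × 1,540 = 211.6.
- Total: about 478. Shortfall: (620 − 478)/620 = 23%.

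Dropout would lower this. An assumed loss of 2% to 10% per year gives about 469 to 430.

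**3. Time to 620 events at the same hazards.** About month 44 with 24-month accrual, or about month 41 with 19-month accrual. On the section 13 dates (A = 19, T = 31) about 433 events have occurred by the close.

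**4. Other time bases (24 + 12 months unless stated, no dropout).**

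| Time base of 25%/20% | Events |
|---|---|
| 36 months, as written | 478 |
| 27 months (median follow-up of the trial cited in 2.2) | 619 |
| 24 months (average follow-up in 2.1) | 686 |
| 24 months, on the section 13 dates (19 + 12) | 625 |

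**5. Effect size.** 25% versus 20% implies HR = ln(0.80)/ln(0.75) = 0.776. A 20% reduction in hazard is HR 0.80. With d events in total, power = Φ(½√d·|ln HR| − 1.993), and the events needed for 80% power are 4(1.993 + 0.842)²/(ln HR)².

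| | HR 0.80 | HR 0.776 |
|---|---|---|
| Events needed for 80% power | 646 | 498 |
| Power with 620 events | 78.4% | 87.9% |
| Power with 478 events | 67% | 78% |

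**The case against.** The strongest objection is that section 2.1 makes the trial event-driven and calls 36 months approximate. If events arrive slowly, the planned response is to continue, not to analyse 478 events. This stands. A reader might infer that the plan delivers 67% power instead of 80%; the document does not support that. The 67% needs a cut at month 36 regardless of the event count, a rule stated nowhere. It also pairs an event count derived from risks that imply HR 0.776 with power at HR 0.80; at the matching hazard ratio, 478 events give 78%.

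A second objection is that the time base is ambiguous, because section 2.2 also uses 36 months of follow-up for the study as a whole. If 25% and 20% are crude proportions over the whole study, 693 events are expected and there is no shortfall. That is a possible meaning, but 693 is not 620 either, so the sentence still needs correcting.

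It is also tempting to conclude that 27 months must have been intended, since it gives 619. That is plausible but not established: 24-month risks on the section 13 dates give 625, and unstated dropout allowances could produce similar totals.

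Finally, the 36 months in section 3.2.2 can be read as a fixed study end. It describes each patient's treatment period counted from day 0, and section 13 is a planning timetable. Neither is a stop rule. What remains is that both sit awkwardly with a trial that, on its stated rates, would run to about month 44.

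**Conclusion.** The point holds as an inconsistency among stated planning figures. Under exponential risks, uniform accrual and no dropout, the risks as labelled give about 478 events at month 36, against the 620 expected. The main consequence is duration: about 44 months, or about 41 with 19-month accrual, instead of about 36. Loss of power is conditional on stopping at month 36.

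Separately, the stated 80% power matches neither reading of the effect exactly. At HR 0.80 the gap is under two percentage points and minor by itself; at HR 0.776 the 620 events exceed what 80% power requires. The documents do not show which figure is the mistaken one. The 36-month label, the expected event count and the duration cannot all be right together, and only the sponsor can say which was intended.

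**What to change.** In section 2.2 and the synopsis:
- State the true time base of the 25% and 20% risks. The sponsor should check whether about 27 months was meant, and it should not be written in without that confirmation.
- If 36 months is meant, restate the expectation as about 478 events at month 36 and about 44 months to reach 620. Show the accrual and dropout assumptions behind these figures.
- Name one hazard ratio as the alternative and give its actual power for 620 events: 78.4% at HR 0.80 or 87.9% at HR 0.776.

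In sections 2.1, 3.2.2 and 13, reconcile the approximate 36-month duration, the per-patient 36-month treatment maximum and the timetable dates with the event-driven rule. The reader should be able to see what happens if 620 events have not occurred by those dates.

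The cost is wording and restated figures. The event target, patient number and analysis method are unchanged. If the 36-month rates are confirmed, the stated duration lengthens, with the operational cost that brings.
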